### 8.3.3 Study completion or discontinuation

The following examination is conducted when the subject has completed or discontinued the study. When the study was discontinued due to subject's death, examination before death is used.

- ① Vital sign is checked.
- ② Physical examination is conducted
- ③ Clinicopathologic test (hematologic, hematochemical, lipid, blood coagulation, blood gas, urine test) is conducted.
- ④ Any difference in medication is assessed.
- ⑤ Adverse event is investigated.
- ⑥ Remaining medication is collected, checked and documented.

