## 10. Study discontinuation, drop out, or analysis exclusion criteria

## 10.1 Study discontinuation and drop out criteria

All patients who enrolled in the study should be recorded of the completion of the study, and if the medication is discontinued or observation is stopped, the reason is recorded. The criteria for patient's drop-out are as follows.

- ① Circumstance that violates inclusion/exclusion criteria
- ② Serious adverse events occurred in patients or patients demands to be dropped out of the study due to adverse events.
- ③ Patient or legal guardian demand the discontinuation of the study due to unsatisfactory curative value during the study.
- ④ Severe hemorrhage
- ⑤ Critical violation of study protocol by principal investigator, researcher or patients.
- ⑥ Patients or legal guardian's withdrawal of the consent.
- ⑦ When patients cannot be followed.
- ⑧ When the patient takes a medication that can influence the study result, without the researcher's authorization during study period.
- ⑨ When the patient is decided not fit for the study progression by researchers.

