## 10.2 Disposal of violation on protocol and non-compliance

The principal investigator and researchers should fully recognize and perform the study protocol, hence the protocol is not violated. However, the inevitable violation will be dealt with as follows.

In case of severe protocol violation, researcher should disregard the patient's data from the analysis and the criteria are as follows.

- ① Failure to acquire written consent
- ② Violation of inclusion/exclusion criteria
- ③ Administration of the medication that is prohibited to use in combination during the study.

Other violation of protocol that is decided to be minor and is not thought to influence the study analysis is thoroughly documented with the degree of violation, reason. Afterwards, the violation is evaluated by researcher, funder, monitor, statistician whether the violation has tempered with the study and included in the PP analysis.

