#### 11.1.1 Primary validity assessment variable

Mortality at ICU

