### 11.3 Analysis method

#### 11.3.1 General principal of result analysis

The data retrieved from the patients during the study is analyzed by Safety analysis, ITT (Intent-To-Treat) analysis and PP (Per Protocol) analysis.

The Safety analysis is analysis including all data from patients in futhan group who have taken the medication at least once and no-anticoagulation group

The ITT analysis is analysis including all data from patients who have been confirmed whether he or she is dead or alive in futhan group who have taken the medication at least once and no-anticoagulation group. And when there is a missing value or patient drop out before the study is over, the latest value can be analyzed as data acquired at relevant time (Last Observation Carried Forward Method).

The PP analysis is analysis including the data from patients who have successfully concluded the study protocol.

The data regarding validity is principally analyzed by PP analysis, and additionally analyzed by ITT analysis.

The data regarding safety is principally analyzed by Safety analysis.

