#### (4) Serious AE/ADR

Serious AE/ADR is adverse event or adverse drug reaction that has occurred in any dosage of medication during the clinical study, and is as follows;

- ① Patient's death during the study
- ② Life threatening circumstances (when the patient is exposed to the risk of death by the incidence of reaction)
- ③ When persistent or significant disability or functional deterioration is anticipated.
- ④ When the patient is need to hospitalized or prolong hospitalization period in already hospitalized patient
- ⑤ When causes congenital disability or abnormality
- ⑥ Other medically significant circumstances

Even if it is not listed above, when patient's safety or health is thought to be compromised, under supervision of attending physician and related specialist's opinion, the reaction is considered as serious adverse event and appropriate management is followed accordingly.

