#### 14.10 Management after adverse event

When adverse event occurs, attending doctor is required to execute necessary examination and treatment immediately. When serious adverse event occurs, the study is discontinued and necessary measures are executed immediately and appropriately under advisement of section 12.6.

15. Other provision that is necessary to perform the clinical study safely and scientifically

A storage system to preserve the clinical study data sheet and record is needed to be ready separately and secured. After the result report is completed, archive manager is pointed and related data is needed to be stored for 10 years after completion of clinical study.

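### The per-protocol set is principal for a randomised comparison of ICU mortality, and the drop-out rules can remove patients from it for reasons tied to treatment and to death

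*Protocol*

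**What the plan says.** The primary variable in section 11.1.1 is "Mortality at ICU". Section 11.2.1 checks whether this mortality is 50% and whether it differs significantly between the arms.

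Section 11.3.1 fixes the order of the analyses: "The data regarding validity is principally analyzed by PP analysis, and additionally analyzed by ITT analysis". It defines the first of these in one sentence: "The PP analysis is analysis including the data from patients who have successfully concluded the study protocol". The ITT set of the same section is a modified one. It requires at least one dose in the futhan arm, with no matching condition in the control arm. It also requires confirmed vital status and allows the last observation to be carried forward.

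Section 10, whose title covers analysis exclusion as well as drop-out, lists the drop-out criteria in 10.1. The second is: "Serious adverse events occurred in patients or patients demands to be dropped out of the study due to adverse events". Severe haemorrhage is another, as is a request by the patient or guardian to stop because the effect of treatment is unsatisfactory.

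Section 10.2 lists the severe violations for which data are disregarded: missing consent, an eligibility violation and prohibited medication. For lesser violations, "the violation is evaluated by researcher, funder, monitor, statistician whether the violation has tempered with the study and included in the PP analysis".

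Two further places bear on deaths. Section 12.1 (4) includes "death during the study" among serious adverse events. Section 8.3.3 has a rule beginning "When the study was discontinued due to subject", which refers to the subject's death and says which examination is then used.

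**The concern.** The trial asks whether mortality differs between randomised arms. Randomisation protects that comparison only while patients stay in the arm to which they were assigned. A patient dropped for a serious adverse event, severe bleeding or poor effect has not successfully concluded the protocol and so falls outside the principal set. These events occur after randomisation, can depend on treatment and are likely to predict death. The protocol itself warns, under the general precautions in section 9.1, that the drug can aggravate haemorrhage in extracorporeal use, so losses for bleeding may differ by arm. The trial is open-label (section 4.3), so whoever judges that a patient is unfit to continue knows the arm.

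No non-inferiority or equivalence aim is stated that might explain putting PP first. The 15% in section 6.3.2 is the precision of a single proportion, not a margin. At stake is whether the primary result is still a randomised comparison.

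**Working it through.** **1. The plan's own figures.** Inputs from section 6.3.2: p = 0.50, α = 0.10 (z = 1.645), δ = 0.15, r = 0.05.

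- n = z²·p(1−p)/δ² = 1.645² × 0.25 / 0.0225 = 30.06, rounded up to 31.
- 31 / 0.95 = 32.6, rounded up to 33.

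Both figures reproduce. They allow for a loss of about 2 patients per arm.

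**2. Withdrawal of patients at higher risk.** Let w be the share of an arm withdrawn and m the mortality among those withdrawn. Then

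PP mortality = (p − w·m) / (1 − w).

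The protocol gives neither w nor m; the values below are assumptions. True mortality is 50% in both arms, so any difference is false.

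| w, futhan | w, control | m | PP mortality, futhan | PP mortality, control | False difference |
|---|---|---|---|---|---|
| 10% | 5% | 70% | (0.50 − 0.07)/0.90 = 47.8% | (0.50 − 0.035)/0.95 = 48.9% | 1.2 points |
| 20% | 5% | 80% | (0.50 − 0.16)/0.80 = 42.5% | (0.50 − 0.04)/0.95 = 48.4% | 5.9 points |
| 30% | 10% | 80% | (0.50 − 0.24)/0.70 = 37.1% | (0.50 − 0.08)/0.90 = 46.7% | 9.5 points |

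Exchanging the arms reverses the sign. With w and m equal in both arms the difference disappears, but each arm's mortality is still shifted whenever m differs from 50%. That matters because section 11.2.1 also checks the level of mortality. A 5% loss made up only of deaths gives (0.50 − 0.05)/0.95 = 47.4%.

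**3. Removal of a share f of the deaths in one arm only.** PP mortality is p(1−f)/(1−pf), and 33(1−pf) patients remain.

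- f = 0.25: 0.375/0.875 = 42.9% v 50%, 7.1 points, with 28.9 patients left in that arm. The chance of a false rejection at the nominal two-sided 10% level is about 15%.
- f = 0.50: 0.25/0.75 = 33.3% v 50%, 16.7 points, with 24.8 patients left. The chance is about 35%.

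**4. The literal limit, f = 1 in both arms.** Expected deaths are 0.5 × 33 = 16.5 per arm. About 16 to 17 patients remain, with 0% mortality, and 31/0.5 = 62 per arm would have to be enrolled to keep 31.

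**The case against.** A reader might infer that the main analysis discards the very events it counts: death is a serious adverse event (12.1), serious adverse events are a drop-out criterion (10.1), and a drop-out has not concluded the protocol (11.3.1). The protocol never states that conclusion, and several sections point the other way:

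- Section 10.2, the only list of data to be disregarded, names neither death, nor serious adverse events, nor haemorrhage.
- Section 11.2.2 (4) and (5) measures ICU and hospital stay up to death, and these are efficacy variables too.
- Section 11.2.1 checks mortality against 50%, which makes no sense in a set without deaths.
- Section 11.3.3.2 (6) applies Kaplan-Meier to all subjects.
- Footnote 2 of section 8.1 gives patients who die a closing examination, and the sentence in 8.3.3 concerns which examination to use, not an analysis set.
- Section 6.3.2 allows 5% wastage beside 50% mortality, so the authors evidently did not count deaths as drop-outs.

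This objection stands. Removal of deaths is a consequence the wording permits, not an instruction. The 5% allowance fails only on that literal reading.

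A reader might also infer that PP membership is settled by people who know the outcomes. Section 4.3 supports knowledge of arm; section 10.2 does not say whether the review precedes or follows sight of outcomes.

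Two further points are fair. The withdrawal rates above are not from the protocol. A bias of 5.9 points is also under half the standard error of the difference at 31 per arm, √(2 × 0.25/31) = 12.7 points. Finally, an ITT analysis is already planned, so a discrepancy would be visible. None of this answers the central point: the analysis named as principal conditions on events after randomisation, and that bias, unlike sampling error, does not shrink with more patients.

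**Conclusion.** The concern holds in this form and should be fixed before the primary result is read. As written, the principal efficacy analysis can remove patients after randomisation for reasons tied to treatment and to death, in a trial where arm is known. The size cannot be fixed from the protocol. The withdrawal scenarios give 1.2 to 9.5 points, 5.9 in the middle case, and either arm may be favoured. They assume 50% true mortality in both arms and 70% to 80% mortality among those withdrawn.

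The collapse to about 16 to 17 patients per arm with 0% mortality shows where the literal wording leads. It is not a forecast of what the investigators would do.

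**What to change.** **Section 11.3.1.** Make all randomised patients, analysed as assigned, the principal efficacy set, and PP supportive. Exchanging the two labels is not enough. Remove the one-dose condition that applies to the futhan arm only and the condition of confirmed vital status. State how unknown vital status is handled, instead of excluding those patients or carrying values forward.

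**Section 10.1.** Separate stopping study treatment from leaving the study. Keep vital-status follow-up for patients who meet a criterion, except where consent for follow-up is withdrawn or the patient cannot be traced. State that death is an outcome and never a drop-out.

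**Reconcile** sections 8.3.3, 10.1, 10.2, 11.3.1 and 12.1 (4) so that they agree on how patients who die, bleed severely or have a serious adverse event are counted.

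Section 14.10 ("When serious adverse event occurs, the study is discontinued") and section 12.6 raise a separate contradiction with a mortality endpoint that expects about 2 × 16.5 = 33 deaths. They too must be reconciled; no clinical rule is proposed here.

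The cost is wording in a few sections, with no new visits. The small downside is some dilution of any effect by patients who stop treatment; the supportive PP analysis remains available to examine that.

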#### 11.3.2 Demographic baseline data

The mean, standard deviation, maximum and minimum values are calculated with continuous data regarding demographic and general condition.

### 11.3.3 Validity data

#### 11.3.3.1 Primary validity assessment value

Mortality at ICU is presented.

#### 11.3.3.2 Secondary validity assessment value

(1) Mortality within hospital

Mortality within hospital is presented.

(2) Mortality at 28 days after initiation of CRRT

Mortality at 28 days after initiation of CRRT is presented.

(3) CRRT duration

The mean, standard deviation, maximum, minimum values of CRRT duration in each group are presented.

(4) ICU hospitalization period

The mean, standard deviation, maximum, minimum values of ICU hospitalization period after ICU initiation in each group are presented.

(5) Hospitalization period

The mean, standard deviation, maximum, minimum values of hospitalization period after CRRT initiation in each group are presented.

(6) Survival

Survival rate at 28 days after initiation of CRRT is calculated using Kaplan-Meier analysis with data of all subjects in the clinical study including censored data. Also, Kaplan-Meier curve is presented as graph, and median survival time of each group is presented.

(7) Filter life span

The mean, standard deviation, maximum, minimum values of filter life span which is changed during the study in each patient are presented.

(8) Blood loss

The mean, standard deviation, maximum, minimum blood loss during each filter change in CRRT with each patient are presented.

(9) Transfusion

The mean, standard deviation, maximum, minimum values of transfusion during CRRT in each patient are presented.

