### 6.3.2 Estimation basis

Primary end point of this clinical study is to evaluate the mortality of Futhan group and compare it to mortality of no-anticoagulation group.

Generally, the mortality of CRRT patients in ICU is known to be roughly 50% [1,4,5].

Thus, we anticipate the mortality in futhan group as 50% and assume the tolerance as 15% to estimate actual mortality. Also, we will add the same number of no-anticoagulation subjects to compare with futhan group on mortality.

Level of significance, ( $\alpha = 0.1$ )

Allowable limits of error for mortality are 15%. ( $\delta=0.15$ )

Considering the patient's severity in ICU, wastage rate is set at 5%. ( $r = 0.05$ )

Hence, necessary number of subjects is calculated after the following formula;

$$n_t = \frac{Z_{1-\alpha/2}^2 p(1-p)}{\delta^2}$$

By this formula, we estimate necessary number of subjects and calculate the final number of subjects by considering drop-out rate using the following formula.

$$n = \frac{n_t}{1-r}$$

The necessary number of subjects is 31 patients per group, and considering the 5% drop out rate, the final number would be 33 patients per group.

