## 7. Clinical study method

## 7.1 Clinical study design

This study is single center, randomized, open clinical study to compare mortality, patients' recovery, safety using nafamostat mesilate and no-anticoagulation during CRRT in ICU patients who has hemorrhagic tendency that prohibits usage of heparin.

When ICU patients with hemorrhagic tendency that needs CRRT who fits inclusion/exclusion criteria voluntarily agrees to participate in the study, patients who fit the inclusion criteria by subject compatibility result are randomly assigned to each group. Since CRRT duration can be different due to patient's condition, nafamostat mesilate administration will be continued until CRRT is discontinued. Afterwards, mortality after 28 days of CRRT discontinuation and renal recovery at 1st outpatient department visit will be compared between each group.

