#### 11.2.2 Secondary validity assessment variables

(1) Mortality in hospital

We will check whether the patients' mortality in hospital after CRRT is 50%, and additionally whether there is any statistical significant difference between two groups.

(2) Mortality at 28 days after initiation of CRRT

We will check whether the patients' mortality at 28 days after initiation of CRRT is 50%, and additionally whether there is any statistical significant difference between two groups.

(3) CRRT duration

We will check the duration of CRRT at ICU between the two groups.

(4) Hospitalization period in ICU

We will check the patients' duration within ICU until recovery to general ward or death.

(5) Hospitalization period

We will check the patients' duration within hospital until discharge or death.

(6) Survival period

We will calculate the survival 28 days after CRRT in both groups. Each patient's survival period is sought to calculate median survival time.

(7) Filter life span

We will check each filter life span during CRRT when CRRT is discontinued and calculate average filter life span.

(8) Blood loss

We will check blood loss at filter change during CRRT.

(9) Transfusion

We will check the amount of transfusion during CRRT.

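### ICU and hospital stay end at death as well as at recovery and are summarised as raw means, and renal recovery is compared among surviving outpatient attenders, so between-arm differences can reflect deaths rather than benefit

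*Protocol*

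**What the plan says.** **End of the clocks.** Section 11.2.2 measures "duration within ICU until recovery to general ward or death", and ends hospital stay at discharge or death. It gives no end rule for CRRT duration and defines transfusion as the amount during CRRT. Section 8.2.5 provides for patients who die while on CRRT, so these two can also be ended by death.

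**Start of the clocks.** Section 11.3.3.2 (4) reads "values of ICU hospitalization period after ICU initiation in each group are presented". Item (5) counts hospital stay from the start of CRRT.

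**Summary measure.** All four outcomes get mean, SD, maximum and minimum. For CRRT duration: "The mean, standard deviation, maximum, minimum values of CRRT duration in each group are presented". For transfusion: "minimum values of transfusion during CRRT in each patient are presented". No item says how deaths are treated. Only survival, item (6), has a method for incomplete follow-up (Kaplan-Meier with censoring).

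**Purpose.** Section 3.1.2 says CRRT duration, ICU and hospital stay and transfusion are compared between the two groups.

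**Expected mortality.** Section 6.3.2: "the mortality of CRRT patients in ICU is known to be roughly 50" per cent.

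**Renal recovery.** Section 7.1 says that recovery at the first "outpatient department visit will be compared between each group". Sections 8.2.14 and 8.3.4 place the creatinine check at that visit, on the routine outpatient schedule. Dialysis status at discharge is also recorded. Renal recovery is not among the nine secondary variables in section 11.1.2.

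**The concern.** A stay that ends in the ward and a stay that ends in death have opposite meanings, yet the stated definition gives both only their length. When about half the patients are expected to die, the mean mixes the two in proportions that depend on treatment if treatment affects mortality. An arm with more deaths can then show a shorter mean ICU or hospital stay with no patient having recovered sooner. Transfusion totals accumulate over CRRT time and can shrink in the same way.

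Renal recovery has a related problem. Patients who die, or who do not return to the clinic, supply no value. The groups compared are survivors who attend, selected after randomisation and seen at no fixed time.

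At stake is the reading of the secondary efficacy results: a shorter stay, less transfusion or better renal recovery could be credited to an arm that merely lost more patients.

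**Working it through.** **1. The plan's own figure.** Inputs from section 6.3.2: alpha 0.1, p = 0.5, delta = 0.15, drop-out 5%.

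- n = 1.645² × 0.5 × 0.5 / 0.15² = 30.06, rounded up to 31.
- 31 / 0.95 = 32.6, rounded up to 33.

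Both stated figures reproduce, so 50% mortality and 31 analysed per arm are used below.

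**2. Shift in a raw mean, with stays by outcome held fixed.** Let S and D be the mean stay of survivors and of deaths, and m the mortality.

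- Mean stay = (1 − m)S + mD.
- Change when m rises by 0.10 = −0.10 × (S − D).

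The protocol gives neither S nor D. With assumed S = 14 and D = 7 days:

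- m = 0.50: 0.5 × 14 + 0.5 × 7 = 10.5 days.
- m = 0.60: 0.4 × 14 + 0.6 × 7 = 9.8 days.

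| Assumed gap S − D (days) | Change in mean per 10 points of mortality (days) |
|---|---|
| 14 | −1.4 |
| 7 | −0.7 |
| 0 | 0 |
| −7 | +0.7 |

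**3. A second illustration, in which extra deaths also shorten the stays.** Assume constant hazards, with the same hazard r of leaving the ICU alive in both arms. Only the death hazard differs.

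- Mean stay = (1 − m)/r, so the ratio between arms is (1 − m1)/(1 − m0), whatever r is.
- Against 50% mortality, arms with 55%, 60% and 65% have 0.90, 0.80 and 0.70 times the mean stay.
- At r = 0.05 per day: 0.50/0.05 = 10.0 days against 0.35/0.05 = 7.0 days at 65%.
- By simulation with 31 per arm, the more lethal arm has the shorter observed mean in about 66%, 81% and 92% of trials.

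Here survivors and deaths within an arm have equal mean stays, yet the means still differ between arms, because a higher death hazard removes patients sooner. The zero shift in step 2 therefore holds only if S and D do not themselves change with mortality.

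**4. Same illustration with death scored zero.** ICU-free days to day 28, 50% against 65% mortality:

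- r = 0.03: 7.2 against 6.1.
- r = 0.05: 9.3 against 7.4.
- r = 0.10: 11.5 against 8.6.

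The more lethal arm now ranks worse throughout this range.

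**5. Can the mortality result warn the reader?** Power for 50% against 65% with 31 per arm is about 32% at two-sided 0.1, and 22% at 0.05.

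**6. Renal recovery.** With 33 per arm and 50% mortality, 0.5 × 33 = 16.5, so about half of each arm can never supply an outpatient value. As an example with assumed rates, suppose 70% of survivors recover at 50% mortality and 80% at 65% mortality. Among survivors the more lethal arm looks better. Among all randomised, 0.50 × 0.70 = 35% against 0.35 × 0.80 = 28%, and the order reverses.

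**The case against.** **Direction is not established.** A reader might infer that early death shortens every duration and lowers transfusion, so that harm must read as benefit. The protocol does not support that. It gives no stay or transfusion figures by outcome. Recovering patients come off CRRT, while dying patients may stay on it and bleed; with a negative gap the shift in step 2 reverses. Nor does the protocol say that shorter is better. This stands: the bias is possible, and its sign and size are unknown.

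**Death as the end point is explicit only for ICU and hospital stay.** For CRRT duration and transfusion it is an inference from section 8.2.5. This stands.

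**The ICU clock.** A reader might infer that ICU stay runs from ICU admission, before randomisation. The wording permits this, but beside item (5) it may equally be a slip for CRRT initiation. Only the ambiguity can be claimed.

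**Deaths are not hidden.** ICU mortality is the primary endpoint, and hospital mortality, 28-day mortality and survival are also presented. This stands in part: the counts will be visible, but low power means an imbalance may be dismissed as non-significant.

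**The outputs are descriptive and the rest belongs in the SAP.** Section 11.3.3.2 says only that values are presented. But section 3.1.2 says they are compared, and the protocol itself fixes the end of each stay and the summary measure. The detail is not simply left open.

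**Renal data are not limited to the clinic visit.** Dialysis status at discharge is also recorded. This stands and makes the remedy feasible, but that status too exists only in survivors.

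**Conclusion.** The concern holds in a limited form. ICU and hospital stay, as defined and summarised, do not separate death from recovery, and they are listed as between-group comparisons in a population with about 50% expected mortality. CRRT duration and total transfusion share the problem by implication. The shift per 10 points of mortality is 0.1 times the survivor-minus-death gap when stays by outcome are fixed: 0.7 days for an assumed 7-day gap, zero for none, reversed for a negative one. The larger ratios of 0.70 to 0.90 rest on constant hazards and an equal hazard of leaving the ICU alive, neither of which comes from the protocol.

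The renal comparison in section 7.1 is restricted to surviving attenders and is not a comparison of the randomised groups.

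It does not follow that the more lethal arm will look better, or that excess deaths would go unreported. These are secondary outcomes; the case for change is that their interpretation could be reversed and the remedy is cheap.

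**What to change.** - **Between-group comparison.** Use days alive and free of CRRT, of ICU and of hospital to day 28 from CRRT initiation. Score death by day 28 as zero and compare by a rank test. Base the count on the index admission unless readmission dates are available.
- **Raw stays.** Keep them as description, split by survivors and deaths. Start ICU and hospital stay at the same point, and reconcile the two start points in section 11.3.3.2 (4) and (5).
- **Transfusion.** Report the total together with vital status. Units per CRRT day may be added as description only: the denominator arises after randomisation, so the rate does not remove truncation by death.
- **Renal outcome.** Analyse alive and off dialysis at hospital discharge among all randomised patients, and keep the outpatient creatinine as description. State the denominator expressly, because section 11.3.1 makes the per-protocol set the main one for efficacy.

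**Cost.** Mostly wording. Vital status at day 28 and dialysis status at discharge are already planned. CRRT, ICU and hospital dates to day 28 must be confirmed on the case report form. Readmissions and CRRT restarts after discharge are not planned to be captured, hence the index-admission rule. The composite is also less familiar to readers than mean length of stay.

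### 28-day mortality and 28-day survival are one quantity, but the protocol bases them on different patients and different handling of unknown status, so the two results can disagree

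*Protocol*

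**What the plan says.** Section 11.1.2 of the protocol lists 28-day mortality as secondary variable 2 and survival as variable 6. Section 11.3.3.2 then states the output for each.

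- Item 2: "Mortality at 28 days after initiation of CRRT is presented". No analysis set is named.
- Item 6: the survival rate at day 28 from the start of CRRT is to be "calculated using Kaplan-Meier analysis with data of all subjects in the clinical study including censored data". A curve and a median survival time are also required.

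The general rule in section 11.3.1 is: "The data regarding validity is principally analyzed by PP analysis, and additionally analyzed by ITT analysis". The two efficacy sets are defined there.

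- PP: "The PP analysis is analysis including the data from patients who have successfully concluded the study protocol".
- ITT: limited to "patients who have been confirmed whether he or she is dead or alive", with at least one dose required in the futhan arm. Missing values and early drop-outs may be filled by last observation carried forward (LOCF).

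**The concern.** With complete follow-up and one set of patients, the day-28 Kaplan-Meier value is exactly one minus the 28-day mortality. Under section 11.3.3.2 the two items share the event (death), the origin (start of CRRT) and the horizon (28 days). They do not share a population or a rule for unknown status.

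The difference need not be random. Section 10.1 makes serious adverse events and severe hemorrhage grounds for drop-out. Section 10.2 removes from the analysis patients given prohibited medication. Who is left in PP can thus depend on how ill the patient was, whereas item 6 keeps everyone.

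At stake is a report with two headline answers to one question in each arm, and no statement of which one stands. In an open-label trial that leaves room to choose after the data are seen.

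**Working it through.** **1. The plan's own figures.** Section 6.3.2 gives alpha 0.10 (two-sided in the formula), p = 0.50, delta = 0.15 and 5% loss.

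n = 1.645² × 0.50 × 0.50 / 0.15² = 30.06, rounded up to 31. Then 31 / 0.95 = 32.6, rounded up to 33. Both stated sizes reproduce. The planned loss is 33 − 31 = 2 patients per arm.

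**2. The sets side by side.**

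| | Item 2, principal (PP) | Item 2, additional (ITT) | Item 6 |
|---|---|---|---|
| Patients | completed the protocol | vital status confirmed; futhan dosed at least once | all subjects |
| Status not known at day 28 | not addressed | LOCF allowed | censored |

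Item 6 matches neither column.

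**3. Effect of different patients.** Assumptions: one arm of 33, k patients outside PP, about half of the PP patients dead by day 28 (d deaths), all status known. PP mortality is d / (33 − k). Mortality in all 33, which is what item 6 would imply, lies between d / 33 (all excluded patients survive) and (d + k) / 33 (all die).

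| k | PP | All 33, lowest | All 33, highest | Largest gap |
|---|---|---|---|---|
| 2 (planned) | 15/31 = 48.4% | 15/33 = 45.5% | 17/33 = 51.5% | 3.1 points |
| 4 | 14/29 = 48.3% | 14/33 = 42.4% | 18/33 = 54.5% | 6.3 points |
| 6 | 13/27 = 48.1% | 13/33 = 39.4% | 19/33 = 57.6% | 9.4 points |

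The gap can go either way.

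**4. Effect of different handling of unknown status, same 33 patients.** Assumptions: 16 deaths evenly spaced over days 1 to 27; c further patients last seen alive shortly after day 3 (2 deaths before, 14 after) or day 14 (8 before, 8 after). LOCF counts these c patients as alive, so mortality is 16/33 = 48.5% throughout. With a deaths before the censoring time and b after, Kaplan-Meier survival at day 28 is

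S = [(33 − a) / 33] × [(33 − a − c − b) / (33 − a − c)].

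For c = 2, censored after day 3: S = (31/33) × (15/29) = 0.486, mortality 51.4%. The same patients censored after day 14: S = (25/33) × (15/23) = 0.494, mortality 50.6%.

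| c | LOCF | Kaplan-Meier, censored after day 3 | Kaplan-Meier, censored after day 14 |
|---|---|---|---|
| 2 | 48.5% | 51.4% | 50.6% |
| 4 | 48.5% | 54.8% | 53.1% |
| 6 | 48.5% | 58.7% | 56.1% |

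The gap is 2 to 3 points with two unknown and up to about 10 points with six. Adding the ITT analysis therefore does not in itself reconcile the two items.

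**5. Zero case.** With k = 0 and c = 0, and every futhan patient dosed, all the estimates coincide.

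**The case against.** The case on the other side has real force, and several stronger readings fall to it.

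- A reader might infer that 28-day mortality is reported in PP only. It is not: ITT is additional. If all status is known and all futhan patients are dosed, ITT mortality equals the Kaplan-Meier result. With 17 deaths in 33, both give 51.5%. In that case the gap is the ordinary PP-versus-ITT difference.
- A reader might infer a gap of 15 points or a reversed direction between arms. Both can be constructed. Removing eight deaths from 17/33 leaves 9/25 = 36.0%. Removing four leaves 13/29 = 44.8%, against a control arm at 16/33 = 48.5%. These cases take out only deaths and only from futhan. The first needs 8 of 33 (24%) outside PP, and the second starts from arms one death apart. Nothing in the protocol makes them likely.
- A reader might measure the gap against the protocol's 15%. In section 6.3.2 that is the half-width for estimating one group's mortality, not a tolerance for disagreement between analyses.
- A reader might infer that the ITT rule removes every patient who would be censored. Confirmation of vital status carries no time point, so a patient last known alive at discharge before day 28 may qualify. Survivors at day 28 are censored too.
- Death is itself a serious adverse event under section 12.1(4), so a reader might infer that all deaths leave PP. In a trial planned around 50% mortality that cannot be the intent, and the point does not need it.

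It is also fair to say that item 6 may be a deliberate exception to the general rule, and that it adds a curve and a median. The protocol does not call it an exception, however, nor say which 28-day figure prevails. What remains is a mismatch between stated rules, not a detail left to an analysis plan.

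**Conclusion.** The point holds as a conflict of analysis sets for one secondary outcome. The principal 28-day mortality comes from PP and the 28-day survival rate from all subjects with censoring. The additional ITT result follows a third rule. Because PP exclusion can be related to prognosis, the two headline results can differ systematically.

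The size is modest at planned losses: about 3 points per arm with two of 33 patients excluded or unknown. It reaches roughly 6 to 9 points with four to six PP exclusions, and is nil with no exclusions and complete day-28 status. The numbers excluded or unknown, the timing of deaths and the roughly 50% mortality in PP are illustrative assumptions. That PP applies to item 2 follows from section 11.3.1, not from the item's own wording. The shared origin is that of section 11.3.3.2; section 7.1 dates the 28 days from the end of CRRT, a separate inconsistency on which this point does not depend.

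The documents do not support a claim that the results will conflict, or that the direction of the comparison will reverse. The change is worth making because it is cheap and removes a choice between two results.

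**What to change.** In sections 11.3.1 and 11.3.3.2:

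1. Name all randomised patients, by assigned group, as the principal set for both item 2 and item 6.
2. Base both on the day-28 vital status that sections 8.2.15 and 8.3.4 already plan to collect, and state that item 2 is one minus the day-28 value of item 6 when status is complete.
3. Do not carry a status of alive forward by LOCF. Censor at last contact only patients whose day-28 status stays unknown, and take item 2 from the same Kaplan-Meier estimate.
4. Add a best-case and worst-case analysis for unknown status. Follow-up runs to discharge (section 8.1, note 7) and no extra visit is planned (section 8.3.4), so censoring at discharge may be informative and could push the Kaplan-Meier mortality up. With 16 known deaths in 33 and two unknown, the bounds are 16/33 = 48.5% and 18/33 = 54.5%.
5. Keep the PP version as a labelled sensitivity result.

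The cost is a few sentences, slightly more analysis work and no new visit. Reported 28-day mortality may move in either direction. The change does not settle which set should lead for ICU mortality, the primary endpoint.
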